#### Sensitivity analysis

To account for potential confounders, a multivariable linear regression analysis will be performed, adjusting for covariates including gender, age, marital status, educational background, and baseline ISI scores.

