**Methods:**

This will be a two-armed, parallel group, randomized controlled study with 80 CID patients. The participants will be randomized to either the iMBCT-I program or the sleep hygiene education (SHE) program at an allocation ratio of 1:1 via simple randomization. Assessments will be carried out at baseline, at the end of the intervention (week 8) and at the follow-up time (week 20). The primary outcome was insomnia severity at week 8. Statistical analyses will follow the intention-to-treat (ITT) principle.

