### Sample size

With reference to the results of a large-scale randomized controlled trial conducted by Lee M. R. which compared the effects of online CBT-I with SHE on chronic insomnia patients, we estimated that the ISI score reductions in the iMBCT-I group and the SHE group were 7.7 and 3.1, respectively, with a common standard deviation of 5.5 (42). Assuming an alpha level of 0.05 and a power level at 0.9, the calculated minimum sample size was 30 participants per group. Estimating a dropout rate of 20%, we plan to recruit 80 participants in total.

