## Statistical methods

### Statistical methods for primary and secondary outcomes

The statistical analyses will follow the intention-to-treat (ITT) principle. Missing values will be handled using a last observation carried forward (LOCF) analysis. Descriptive statistics at baseline will be computed using frequencies and percentages for categorical variables, means with standard deviations (SD) or medians with lower and upper quartiles for continuous variables. Tests of statistical significance between groups will be made. Clinical remission rate of insomnia in week 8 and week 20 will be calculated. All analyses will be conducted using IBM SPSS 25.0. A two-tailed p-value < 0.05 will be considered statistically significant.

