#### Primary outcome analysis

Changes between groups in ISI scores from baseline to week 8 will be evaluated using paired t-tests (for normally distributed data) or paired Mann-Whitney U tests (for non-normally distributed data). The between group effect sizes (Cohen’s d) will be calculated using the mean differences from baseline and the SDs of the two groups at week 8.

A Univariable linear regression will be conducted to evaluate the effect of MBCT-I on ISI score reduction. The change in ISI scores from baseline to week 8 will be used as the dependent variable, while the intervention group (MBCT-I vs. SHE) will be included as the independent categorical variable. The regression coefficient (B) will represent the estimated effect of MBCT-I on ISI score reduction.

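### The primary ISI analysis is an unadjusted change-score comparison; moving baseline ISI into the primary model would improve precision at almost no cost

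*Protocol article*

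**What the plan says.** The Primary outcome analysis section plans a between-group test of ISI change from baseline to week 8, and then a regression: "A Univariable linear regression will be conducted to evaluate the effect of MBCT-I on ISI score reduction". Group is its only independent variable, and its coefficient is to be read as the treatment effect.

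Baseline ISI appears by name as a covariate in one place, the Sensitivity analysis section: "a multivariable linear regression analysis will be performed, adjusting for covariates including gender, age, marital status, educational background, and baseline ISI scores". The reason given there is control of potential confounders.

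The Secondary outcome analysis section adds a mixed model for repeated measures that includes ISI up to week 20. It has baseline covariates, but they are not named.

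The abstract states that participants are allocated "at an allocation ratio of 1:1 via simple randomization", and Assignment of interventions repeats this. No stratification on baseline ISI is stated. Entry requires ISI above 14, and Table 1 schedules the ISI at screening, baseline, week 8 and week 20.

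**The concern.** A change score subtracts the whole baseline value, so it treats the slope of week-8 ISI on baseline ISI as exactly 1. A model that includes baseline ISI estimates that slope. If the true slope is not 1, the change-score analysis has a larger residual variance than it needs. Part of any chance difference in baseline ISI between the arms also passes into the estimated effect.

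With 80 people and unstratified simple randomisation, the design does not restrain such a difference. The article already plans the adjusted model but gives it the subordinate role. At stake are the width of the primary confidence interval and the robustness of the primary estimate to the baseline split that happens to occur.

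**Working it through.** **Inputs from the Sample size section.** "we estimated that the ISI score reductions in the iMBCT-I group and the SHE group were 7.7 and 3.1, respectively", so the target difference is 7.7 − 3.1 = 4.6 points. The common SD is 5.5, read here as the within-arm SD of the reduction. "Assuming an alpha level of 0.05 and a power level at 0.9". Statistical methods sets the test as two-sided at 0.05.

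**Reproducing the plan's figure.** n per arm = 2 × (1.960 + 1.282)² × 5.5² / 4.6² = 30.04, which rounds up to 31; the noncentral-t calculation gives 32. The article states "the calculated minimum sample size was 30 participants per group", which agrees closely. Allowing for 20% dropout, 32 / 0.8 = 40 per arm, or 80 in total. With 32 per arm the unadjusted change-score test has power 0.909 and a 95% CI half-width of 2.75 points.

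**Assumptions (not in the article).** Baseline SD s0 = 3 to 4, and baseline to week-8 correlation r = 0.3 to 0.7. The SD of change is held at 5.5.

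**Formulas.**
- Week-8 SD: s1 = r·s0 + √(5.5² − s0²(1 − r²))
- Slope: r·s1/s0
- Variance ratio, adjusted to change score: s1²(1 − r²)/5.5²
- Standard error of the chance baseline difference at 32 per arm: s0·√(2/32)
- Shift in the estimated reduction for a one-standard-error imbalance: (1 − slope) × that standard error

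**Worked case, s0 = 4 and r = 0.3.** s1 = 1.2 + √(30.25 − 14.56) = 5.16. Slope = 0.3 × 5.16 / 4 = 0.39. Variance ratio = 5.16² × 0.91 / 30.25 = 0.80. Standard error = 4 × 0.25 = 1.00, so the shift is 0.61 points.

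| s0 | r | slope | variance ratio | adjusted SD | power, 32 per arm | shift (points) |
|---|---|---|---|---|---|---|
| 3 | 0.3 | 0.56 | 0.94 | 5.34 | 0.924 | +0.33 |
| 3 | 0.5 | 1.06 | 1.00 | 5.50 | 0.909 | −0.04 |
| 3 | 0.7 | 1.67 | 0.87 | 5.12 | 0.943 | −0.50 |
| 4 | 0.3 | 0.39 | 0.80 | 4.92 | 0.957 | +0.61 |
| 4 | 0.5 | 0.78 | 0.98 | 5.43 | 0.915 | +0.22 |
| 4 | 0.7 | 1.31 | 0.95 | 5.36 | 0.922 | −0.31 |

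A positive shift means that the arm starting higher shows the larger reduction; a negative shift means the reverse. Over this range the adjusted half-width is 2.46 to 2.75 points.

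**Equal-SD case.** If the baseline and week-8 SDs are equal, the variance ratio is (1 + r)/2, which is 0.65 to 0.85 for r = 0.3 to 0.7. With a change SD of 5.5, this requires a baseline SD of 5.5/√(2(1 − r)): 4.6 at r = 0.3, 5.5 at r = 0.5 and 7.1 at r = 0.7. For comparison, scores spread evenly over 15 to 28, the range the entry rule allows on this seven-item, 0-to-4 scale, have an SD of about 4.0.

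**The case against.** The planned analysis is valid in this respect. Under randomisation the unadjusted change contrast is unbiased on average, and it matches the quantity used to size the trial. It already uses baseline ISI through the subtraction, and the trial is described as exploratory. When the slope is near 1, adjustment gains nothing. The analysis is also intention-to-treat with last observation carried forward, so about 40 per arm would enter it rather than 32. With the same effect and SD, power at 40 per arm is 0.959 unadjusted and 0.959 to 0.985 adjusted. ISI is analysed again in the secondary mixed model, and the article labels which analysis is primary, so a disagreement would not leave the primary result undefined.

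All of this stands, and it limits the point to efficiency. It does not remove it. The mixed model is secondary and its covariates are unnamed, so it does not change the primary result. The variance ratio does not exceed 1 in any scenario, and the sponsor cannot know beforehand that the slope will be close to 1.

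A reader might also infer that the whole of a chance baseline difference enters the estimate, always in favour of the arm that starts higher. The documents do not support that: only (1 − slope) of it remains, and the sign reverses when the slope exceeds 1.

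**Conclusion.** The point holds as an improvement in precision that costs almost nothing. Assuming a change SD of 5.5, a baseline SD of 3 to 4 and a correlation of 0.3 to 0.7, baseline adjustment removes about 0 to 20% of the variance. Power at 32 per arm is about 0.91 to 0.96, against 0.91. A one-standard-error baseline imbalance moves the unadjusted estimate by about 0 to 0.6 points in absolute value, against a target of 4.6.

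A reader might infer a gain of 15 to 35% from the usual (1 + r)/2 rule. That needs equal baseline and week-8 SDs, and hence baseline SDs of 4.6 to 7.1, which sit poorly with entry restricted to ISI above 14. A reader might also infer that the primary test is biased or the trial too small. Neither follows: the stated sample size reproduces, and power is about 0.91 without adjustment. The role of each model is clear from the text; the size of the gain is uncertain because the article gives neither the correlation nor the separate SDs.

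**What to change.** Before any outcome data are seen by arm, make these changes:

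- Name one primary analysis: the linear model of week-8 ISI (or ISI change, which gives the same treatment coefficient once baseline is included) on arm plus baseline ISI.
- Make the unadjusted comparison supportive.
- Keep the model that also includes gender, age, marital status and education as sensitivity.
- Adjust each secondary scale for its own baseline value, and name that covariate in the mixed model.
- Give the reason for baseline adjustment as precision and chance imbalance, not confounding.

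The cost is one degree of freedom and wording in the protocol and analysis plan. Baseline ISI is already scheduled for every participant and already in a planned model, so no new data or participants are needed.

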#### Secondary outcome analysis

Changes between groups in scores of PSQI, FFMQ, PHQ-9, GAD-7, SF-12, ATSPPH-SF and DBAS-16, insomnia remission rate and all sleep parameters values from baseline to week 8 will be evaluated using paired t-tests (for normally distributed data)/Mann-Whitney U tests (for non-normally distributed data). Mixed-effect models for repeated measures will be used to evaluate the effects of the online MBCT-I on scores of ISI, PSQI, FFMQ, PHQ-9, GAD-7, SF-12, ATSPPH-SF and DBAS-16 as well as all sleep parameters values over time (from baseline to week 20). The model will include treatment group, time, treatment-by-time interaction and baseline covariates.

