### Eligibility criteria

To be included, participants must fulfil the following criteria (1): Aged between 18 and 65 years with normal speech and cognitive functions, defined as a total score of >25 on the Montreal Cognitive Assessment (MoCA) (36) (2); having chronic insomnia disorder based on Insomnia Severity Index (ISI) >14 and DSM-5 diagnostic criteria that include (a) difficulties initiating and/or maintaining sleep, defined as sleep onset latency (SOL) and/or wake time after sleep onset (WASO) greater than 30 minutes, or early-morning awakening with inability to return to sleep; (b) sleep difficulty being present at least 3 nights per week and for a period of at least 3 months; (c) severe impairment of daytime functioning (3); being willing to complete the online MBCT-I or SHE program (4); agree to maintain the dosage and frequency of sleep medication throughout the study or discontinue usage for at least 2 weeks (washout period) prior to study enrollment among those who use sleep medication; and (5) voluntarily signing the informed consent form.

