### Outcomes

#### Primary outcome measures

In this study, the Insomnia Severity Index (ISI) will be used to measure the severity, nature and impact of insomnia (43). It consists of 7 items and is rated on a 5-point scale ranging from 0 (no problem) to 4 (very severe problem). A total score of 8–14 suggests subclinical insomnia, and a total score over 14 indicates clinical insomnia. A reduction in ISI scores of 8 or more points from baseline is regarded as a response to treatment, and an absolute score on the ISI of 7 points or less is regarded as remission (44, 45). The Chinese version of ISI was translated and validated by Yang et al. and its Cronbach’s α was 0.94 (46). And it is supported to be a valid outcome measure for CBT-I by literature (47).

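### The yes/no remission outcome is assigned paired t-tests or Mann-Whitney U tests; it should be compared between arms as two independent proportions

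*Protocol article*

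**What the plan says.** All references are to the protocol article.

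- **Secondary outcome analysis.** The list of outcomes for between-group comparison runs "Changes between groups in scores of PSQI, FFMQ, PHQ-9, GAD-7, SF-12, ATSPPH-SF and DBAS-16, insomnia remission rate", and the sentence continues "insomnia remission rate and all sleep parameters values from baseline to week 8 will be evaluated using paired t-tests", with Mann-Whitney U tests as the alternative for non-normal data. Remission is thus handled like the questionnaire totals and sleep parameters, as a change from baseline to week 8.
- **Primary outcome measures.** Remission is a threshold on the ISI: "an absolute score on the ISI of 7 points or less is regarded as remission".
- **Eligibility criteria.** Entry requires "having chronic insomnia disorder based on Insomnia Severity Index (ISI) >14".
- **Trial design; Assignment of interventions.** There are two parallel arms, 1:1, with simple randomization and no matching.
- **Statistical methods for primary and secondary outcomes.** "Clinical remission rate of insomnia in week 8 and week 20 will be calculated". The same paragraph says in general terms that groups will be tested for significance. It names no method for a proportion, and it sets LOCF for missing values.
- **Secondary outcome analysis, second sentence.** "Mixed-effect models for repeated measures will be used to evaluate the effects of the online MBCT-I on scores of ISI, PSQI, FFMQ" opens the list of outcomes for the longitudinal model. Remission is not on that list.

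**The concern.** The article does name a method for remission, and the method does not fit. A paired t-test needs paired measurements of a roughly continuous quantity. Remission is a 0/1 status, its baseline value is essentially fixed at zero by the entry criterion, and the participants in the two arms are different, unmatched people. Change in remission from baseline is therefore just week-8 status, and the question to answer is whether the week-8 proportions differ between arms.

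At stake is how remission gets reported. An analyst who follows the paired wording could report a significant remission result that says nothing about iMBCT-I against SHE. An analyst who follows the non-normal branch gets a sound p-value, but is not directed to any size of effect or its uncertainty.

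**Working it through.** **Inputs.** 80 participants, 1:1, taken as 40 per arm (Sample size); two-sided 0.05 (Statistical methods); remission is ISI 7 or less; entry is ISI above 14. The article assumes no remission rates, so every remitter count below is an illustrative assumption.

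**The plan's own figure.** There is none for remission. The sample size for the ISI comparison reproduces: 2 × (1.96 + 1.2816)² × 5.5² / 4.6² = 30.04 per group against the stated 30. Then 30/0.8 = 37.5, so 38 per arm or 76 in all, which 80 covers. Nothing below depends on it.

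**1. Paired t-test read within an arm.** With all baselines at 0 and week-8 proportion m among n participants, the mean change is m and its SE is √[m(1−m)/(n−1)]. So t = √[(n−1)m/(1−m)], on n−1 = 39 df, with critical value 2.02.

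- 3/40: t = √(39 × 0.075/0.925) = 1.78, not significant.
- 4/40: SE = √(0.09/39) = 0.0480; t = 0.10/0.0480 = 2.08, p = 0.044.
- 8/40: t = √(39 × 0.20/0.80) = 3.12, p = 0.003.

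With 8/40 in both arms, each arm gives p = 0.003 although the arms are identical. In 20,000 simulated trials with equal true rates in the two arms, the within-arm test rejects in 58%, 97% and 99.9% at true rates of 10%, 20% and 30%. It carries no information on the difference between arms.

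**2. Paired t-test read across arms.** Take 14/40 against 6/40. The mean difference is 0.20 however people are paired, but the variance depends on the pairing.

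- All 6 SHE remitters paired with iMBCT-I remitters: 8 differences of +1 and 32 of 0; t = 3.12, p = 0.003.
- None so paired: 14 of +1, 6 of −1, 20 of 0; variance (20 − 1.6)/39 = 0.472, SE = √(0.472/40) = 0.109, t = 1.84, p = 0.073.

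The p-value depends on an arbitrary ordering. Also, simple randomization of 80 gives exactly 40:40 with probability C(80,40)/2⁸⁰ = 0.089, so usually the arms could not all be paired.

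**3. Mann-Whitney U on 0/1 data.** Without continuity correction, its squared statistic is the Pearson chi-square times (N−1)/N. For 16/40 against 6/40:

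- pooled proportion 22/80 = 0.275;
- chi-square = 0.25² / (0.275 × 0.725 × 2/40) = 6.27, p = 0.0123;
- times 79/80 = 6.19, p = 0.0128.

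In the simulation above it rejects in 6.0%, 5.3% and 4.7% of trials. The test is acceptable; what does not come with it is a risk difference, ratio or interval.

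**4. Independent proportions.** Risk difference ± 1.96 × √[p₁(1−p₁)/40 + p₂(1−p₂)/40]:

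| Remitters | Risk difference (95% CI) | Chi-square p | Fisher p |
|---|---|---|---|
| 16/40 vs 6/40 | 0.25 (0.06 to 0.44) | 0.012 | 0.023 |
| 12/40 vs 4/40 | 0.20 (0.03 to 0.37) | 0.025 | 0.048 |
| 8/40 vs 8/40 | 0.00 (−0.18 to 0.18) | 1.0 | 1.0 |

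**The case against.** The strongest reply is that the plan's own rule avoids the worst outcome. The t-test is reserved for normally distributed data, a 0/1 variable is never normal, and the rule therefore leads to Mann-Whitney U, which is nearly the chi-square test. The sentence also speaks of changes between groups, so the word paired may simply be loose. This stands. A reader might infer from the 4-in-40 figure that remission will come out significant in both arms whatever the treatment does. The article does not support that: the figure applies only to the paired branch, read within arm.

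A second reply is that the arm rates at weeks 8 and 20 will be calculated, so a crude risk difference is available by subtraction. That also stands. It would be wrong to say that no usable figure could be had; what has no stated source is an interval, and the only comparison named for remission is the mismatched one.

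A reader might also count it as an error that response is defined ("A reduction in ISI scores of 8 or more points from baseline is regarded as a response to treatment") but appears in no analysis section. The Introduction does not list response among the secondary outcomes, no section promises to analyse it, and a condensed article may leave it to the analysis plan.

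Finally, zero remission at baseline is not quite absolute. ISI is taken at screening and again at week 0 (Table 1), so a week-0 score of 7 or less is very unlikely but not strictly excluded.

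**Conclusion.** The point holds as an error of stated method on a secondary outcome in a trial that calls itself exploratory. The paired t-test is wrong for remission on either reading. The Mann-Whitney branch, which the normality rule would select, gives a usable p-value but no estimate or interval. The damage is therefore largest if the paired wording is followed literally, and small, confined to reporting, if the normality rule is followed.

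This rests on 40 per arm, on essentially no remission at baseline, and on illustrative remitter counts. The primary effect estimate, the regression coefficient for ISI change, is unaffected. The paired wording also appears under Primary outcome analysis, but that is a separate matter; what is specific here is a binary outcome placed in a list of continuous ones.

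**What to change.** In Secondary outcome analysis, remove the remission rate from the t-test/Mann-Whitney list and add a sentence to this effect: the proportion in remission (ISI 7 or less) will be compared between arms at week 8 and week 20 as independent proportions, reporting the risk difference with its 95% CI and a chi-square or Fisher's exact p-value. A logistic model with arm and baseline ISI is an optional addition.

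No change to missing-data handling is needed for this point. Under the stated LOCF rule, a participant with no post-baseline ISI carries the baseline score forward and counts as not in remission. One with a week-8 score but none at week 20 keeps the week-8 status.

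The cost is one sentence of wording and trivial analysis work, with no new data and no change to sample size.

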#### Exploratory analysis

In order to identify predictors of effectiveness, subgroup analyses will be conducted to compare the efficacy of iMBCT-I among participants with different characteristics, such as demographics, mindfulness levels (FFMQ) and attitudes towards psychotherapy (ATSPPH-SF). Additionally, the relationship between the number of attended sessions and treatment efficacy will be explored using regression analysis, with session attendance as an independent variable and ISI score reduction as the dependent variable.

Structural equation models will be applied to identify possible mediators and moderators of intervention efficacy such as mindfulness levels (FFMQ) and attitudes towards psychotherapy (ATSPPH-SF) at baseline.

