## Interventions

### Intervention description

#### Intervention group: iMBCT-I

Participants will receive a 12-hour iMBCT-I treatment. MBCT-I consists of weekly 1.5-h sessions over 8 weeks online through the Tencent Meeting, with mindfulness practice as homework six times a week.

The iMBCT-I program was adapted from the original format of Segal et al., which targeted mainly depression and consisted of eight 2.5-hour sessions held on a weekly basis (20). The modification mainly followed the MBCT-I in Wong SY and colleagues’ research, making it tailored for CID patients (22). Due to the limitation that Tencent Meeting displays a maximum of 25 members’ videos per page, we set the maximum group capacity to 20 individuals to ensure that all members can consistently maintain face-to-face interaction online.

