#### Attendance and intervention completion

Retention rate (number and proportion that attended each class) of participants in MBCT-I group are documented. And reasons for non-attendance will be recorded. Participants who attended six or more iMBCT-I sessions will be considered as having completed the intervention. For those who did not complete the intervention, researchers would conduct interviews to inquire about the relevant reasons. In addition, the completion of the sleep diary, actigraphy usage, and the number of sessions attended are collected as indicators of adherence.

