## Data collection and management

Assessments will be conducted at week 0 (baseline), week 8 (post-intervention) and week 20 (3 months after intervention). Details are displayed in **Table 1**.

**Table 1 T1:** Assessment schedule.

Outcome	Measure	Time of assessment			
		Screen	Baseline (week 0)	Post-intervention (week 8)	Follow-up (week 20)
Socio-demographics	SR	X			
CID	MINI	X			
Insomnia severity	ISI	X	X	X	X
Sleep quality	PSQI		X	X	X
Mindfulness level	FFMQ		X	X	X
Depression	PHQ-9		X	X	X
Anxiety	GAD-7		X	X	X
Quality of life	SF-12	X	X	X	X
Attitudes	ATSPPH-SF	X	X	X	X
Dysfunctional beliefs	DBAS-16		X	X	X
Sleep parameters	Actigraphy		X	X	X
Treatment adherence	Number of completed sessions			X	X

SR-self reported measure; MINI- Mini International Neuropsychiatric Interview (MINI) provided by two psychiatrists; ISI- Insomnia Severity Index; PSQI- Pittsburgh Sleep Quality Index; FFMQ- The Five Facet Mindfulness Questionnaire; PHQ-9- The Patient Health Questionnaire-9; GAD-7- The Generalized Anxiety Disorder 7-item scale; SF-12- The 12-item Short Form Health Survey; ATSPPH-SF- The Attitudes Toward Seeking Professional Psychological Help Scale-Short Form; DBAS-16- Dysfunctional Beliefs and Attitudes about Sleep Scale 16-item version.

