### Plans to promote participant retention and complete follow-up

Participants will be fully explained the importance of completing assessment at baseline, post-intervention and follow-up during recruitment. Each participant will receive a notification on the smartphone to complete the assessments online within 2 days. All questions were mandatory to ensure no missing data, and participants may pause and report to the research assistant at any time. Phone reminders will be provided if assessments were not completed on time.

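### Carrying baseline ISI forward gives non-returners a reduction of exactly zero, which tilts the exploratory attendance regression upwards if low attenders are the ones missing at week 8

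*Protocol article*

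**What the plan says.** The opening paragraph of Statistical methods (Statistical methods for primary and secondary outcomes) sets the general rules: "The statistical analyses will follow the intention-to-treat (ITT) principle", and "Missing values will be handled using a last observation carried forward (LOCF) analysis". No other missing-data method is named. The primary, sensitivity, secondary and exploratory analyses follow as subsections, and none makes an exception.

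The Exploratory analysis subsection relates the number of sessions attended to treatment efficacy by regression, "with session attendance as an independent variable and ISI score reduction as the dependent variable". It does not give the time point, the participants included or the handling of missing ISI. The only change score defined is in Primary outcome analysis: "The change in ISI scores from baseline to week 8 will be used as the dependent variable".

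Table 1 lists the ISI at screening, baseline, week 8 and week 20, with nothing between baseline and week 8. The weekly questionnaires described for the control group are not described as ISI. On attendance, "MBCT-I consists of weekly 1.5-h sessions over 8 weeks online through the Tencent Meeting", and "Participants who attended six or more iMBCT-I sessions will be considered as having completed the intervention".

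**The concern.** With this visit schedule, the last ISI before week 8 is the baseline value. For anyone without a week-8 ISI, LOCF sets week 8 equal to baseline, and the reduction is 0 by construction.

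That zero is the outcome in a regression whose predictor is sessions attended. If the missing participants are mostly those who stopped attending, the low end of the attendance axis is filled with zeros while the high end holds real improvements. The fitted slope is then positive even when attendance makes no difference.

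The regression is meant to show whether more sessions go with more benefit. The Discussion says that the exploratory analysis of factors influencing outcomes will help to guide treatment choices, and the Introduction justifies the shorter sessions by better compliance. A dose-response produced by imputation would mislead on both. An exploratory label covers low power and multiplicity, but not a slope produced by the missing-data rule.

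**Working it through.** **Inputs from the protocol article.** Expected ISI reductions are 7.7 and 3.1, SD 5.5, dropout 20% (Sample size). There are 8 sessions, 80 participants are allocated 1:1, so about 40 are in the iMBCT-I arm, and tests are two-sided at 0.05. No figure is given for the attendance regression itself. The sample-size inputs are consistent with the plan's own number: 2 × [5.5 × (1.960 + 1.282) / 4.6]² = 30.04 per group, against the stated 30.

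**Assumptions, not in the protocol.** The true reduction is unrelated to attendance (no dose-response). Sessions follow Binomial(8) with mean 7 for those who stay and mean 2 or 4 for dropouts.

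**Slope by hand.** Let p be the dropout proportion, q the share of dropouts with no week-8 ISI, m the mean true reduction, and D the difference in mean sessions. LOCF lowers the dropouts' mean reduction by qm, so

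slope = p(1 − p) × D × qm / [p(1 − p) × D² + within-group variance of sessions].

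- Dropouts average 2 sessions (D = 5), m = 7.7, q = 1. Numerator: 0.16 × 5 × 7.7 = 6.16. Within-group variance: 0.8 × 0.875 + 0.2 × 1.5 = 1.0. Denominator: 0.16 × 25 + 1.0 = 5.0. Slope: 1.23 ISI points per session.
- Dropouts average 4 sessions (D = 3). Numerator: 0.16 × 3 × 7.7 = 3.70. Denominator: 0.16 × 9 + (0.7 + 0.2 × 2) = 2.54. Slope: 1.46.
- Half of the dropouts return (q = 0.5): the slopes halve, to 0.62 and 0.73.
- Mean reduction 3.1, none return: 2.48 / 5.0 = 0.50 and 1.49 / 2.54 = 0.59.
- All return (q = 0): slope 0.

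**Simulated rate of p < 0.05 with no true dose-response** (n = 40, 20% dropout):

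| Scenario | Rate with LOCF |
|---|---|
| Mean 7.7, no dropout returns | about 77–93% |
| Mean 7.7, half return | about 28–35% |
| Mean 3.1, no dropout returns | about 13–22% |
| All return, or missingness unrelated to attendance | about 5% |

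Repeat runs move these by a few percentage points. One gave 26–35% for half returning and 14–19% for mean 3.1. With mean 7.7 and nobody returning, the rate is 39–59% at 10% dropout and 93–99% at 30%.

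**A different attendance pattern as a check** (stoppers 0–5 sessions, others 6–8, uniform; n = 40, 20% stopping):

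- none return: slope 1.30, rate 97%
- half return: 0.64, 33%
- all return: 0.01, 5.5%
- missingness unrelated to attendance: 0.01, 5.2%
- mean reduction 3.1, none return: 0.52, 15%

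If only 42% attend six or more sessions (the figure the Introduction cites from the earlier face-to-face trial) and the lowest-attending 20% are missing, the slope is 0.86 and the rate 76%.

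**Observed week-8 ISI only.** In this second set the mean slope is about 0 and the rate 4.3–5.5% in every scenario. That result depends on outcome being independent of both dropout and attendance in the simulation.

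**The case against.** The strongest objection is that stopping the sessions is not the same as missing the assessment. The ISI is a short online questionnaire, participants are notified to complete it within 2 days, and "Phone reminders will be provided if assessments were not completed on time". Non-completers are to be interviewed, and the device incentive depends on completing the study. If these measures work, the artefact shrinks or disappears. This stands, and it is why the size can only be given as a range.

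It is also fair that 7.7 is the assumed effect of the whole programme, so crediting it to someone with two sessions may be generous. At 3.1 the artefact is much smaller. This stands too.

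A third objection is that applying LOCF here is an inference, because the heading over the rule names primary and secondary outcomes and a separate analysis plan may refine it. This carries less weight. The rule is the only one stated, the exploratory subsection sits under it, and no exception is made. It is true that the time point is not named. For a week-20 reduction, the zero would apply only to those missing both week 8 and week 20.

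A reader might go further and infer that attendance becomes a proxy for treatment arm because control participants have one session. The document does not support this: class attendance is recorded for the MBCT-I group, and nothing puts control participants into this regression. A reader might also want a complier effect at six or more sessions instead. That would need the doubtful assumption that one to five sessions do nothing, and it would still need the missing outcomes.

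**Conclusion.** The point holds as a conditional one. The zero reduction follows exactly from the visit schedule and the LOCF rule. The positive slope follows only if missing week-8 ISI is concentrated among low attenders who would on average have improved. Under the protocol's 20% dropout, the false-positive rate then runs from about 5% to about 93% in the four main scenarios. The two deciding inputs are how many dropouts return for week 8 and how much they would have improved, and the protocol fixes neither.

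A reader might conclude that the analysis will nearly always show a dose-response, whatever the truth. The document does not support that: it needs no returners and a full 7.7-point improvement among the dropouts, and even then 10% dropout gives only 39–59%.

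The point is minor. The analysis is exploratory, no stated hypothesis concerns session attendance, and the primary conclusion is unaffected.

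**What to change.** In Exploratory analysis, state that the attendance regression:

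- is fitted in the iMBCT-I arm, with baseline-to-week-8 ISI reduction as the outcome;
- uses only participants with an observed week-8 ISI, with no LOCF values;
- is adjusted for baseline ISI;
- is reported with a table of week-8 missingness by number of sessions attended;
- is described as an association and not as a causal effect, because attendance is determined after randomisation.

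The cost is a few lines of wording and no change to trial conduct. The sample for this one analysis is smaller: at 20% missing, about 32 of 40 (40 × 0.8). Observed-case results may still be biased if poor responders leave, and the missingness table lets readers judge that risk.
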